## Abstract

**Background:**

Dementia is a global public health concern, with prevalence projected to reach 78 million individuals by 2030 and 139 million by 2050. Most persons living with dementia reside in community settings and are supported by family caregivers. As caregiving demands grow, caregivers experience significant psychosocial, emotional, and financial burden, including high rates of stress, social isolation, and depressive symptoms. Access to effective support services remains limited, highlighting the urgent need for innovative and accessible caregiver interventions.

**Objective:**

This pilot study first aims to assess the feasibility, acceptability, and tolerability of VR-SIM Carers, a virtual reality (VR)–based psychoeducational training program for family caregivers or care partners of people living with dementia. Second, it will aim to provide a preliminary evaluation of potential impact on caregiver outcomes, including caregiver competence, stress, resilience, empathy, and quality of life. The study is not designed to support causal inference regarding the effectiveness of VR-SIM Carers.

**Methods:**

A mixed methods design will be used with a sample of 30 family caregivers of people living with dementia. Participants will complete 3 immersive, self-paced VR caregiving scenarios—Managing Apathy, Crisis Response, and Refusal of Care—receiving real-time feedback from simulated characters, including clinician and person living with dementia avatars. Primary outcomes (feasibility and educational impact) include recruitment, retention, adherence, usability, acceptability, and tolerability and caregiver competence (Pearlin Caregiving Competence Scale), perceived stress (Cohen Perceived Stress Scale), resilience (Connor-Davidson Resilience Scale), and empathy (Empathy Assessment Scale). Secondary outcomes (preliminary efficacy) include caregiver quality of life (Adult Carer Quality of Life Questionnaire), caregiver burden (Burden Questionnaire), and behavioral symptoms (Neuropsychiatric Inventory, Center for Epidemiologic Studies Depression Scale Short Form) assessed at baseline, postintervention, and 1-month follow-up. Feasibility and user engagement will be evaluated via the 18-item Gaming Use Engagement and Severity Scale, Igroup Presence Questionnaire, qualitative interviews, reflection notes, and open-ended feedback. Quantitative data will be analyzed using repeated-measures ANOVA and paired 2-tailed *t* tests, while qualitative data will be analyzed using an inductive thematic coding framework. Data analyses are descriptive and exploratory only, and no causal claims regarding intervention effectiveness will be made. Consistent with CONSORT (Consolidated Standards of Reporting Trials) guidance for pilot and feasibility studies, caregiver outcomes (eg, competence, stress, resilience, empathy) are treated as exploratory.

**Results:**

The findings from this study will inform the feasibility, acceptability, and educational value of immersive VR for caregiver training, while providing preliminary evidence regarding the efficacy of VR-SIM Carers as a training tool to improve psychoeducation outcomes for family caregivers of people living with dementia and reduce caregiving burden. Data collection commenced in March 2024 with a projected end date of March 2026. As of the submission of the manuscript (December 2025), 21 participants have been enrolled. Data analysis will be completed in April 2026, and the results are expected to be published in fall 2026.

**Conclusions:**

VR-SIM Carers represents an innovative, scalable intervention designed to enhance caregiver preparedness, psychosocial outcomes, and sustainable community–based dementia care. This pilot study will provide critical evidence to guide further development and implementation of VR-based caregiver support programs.

## Introduction

### Background

Dementia is a growing global public health challenge with profound personal, societal, and economic implications. As the world’s population ages, the prevalence of dementia is projected to increase dramatically: in 2019, an estimated 55.2 million people were living with dementia worldwide—a figure expected to rise to 78 million by 2030 and 139 million by 2050 [1]. This demographic shift is mirrored in Canada, where the incidence of dementia is rising alongside the aging population. By 2030, nearly 1 million Canadians are expected to be living with dementia, and this number is projected to double by 2050 [2]. In Canada, approximately 61% of people with dementia reside at home, instead of in long-term care facilities [3]. This trend reflects both the wishes of older adults to age in place and the increasing reliance on unpaid caregivers—primarily family members, friends, and neighbors—to provide daily support [3]. In low- and middle-income countries, where formal care services are often limited, family caregiving is nearly universal; however, even in high-income countries, such as Canada, the majority of people living with dementia continue to rely on unpaid care arrangements [4].

Unpaid caregivers are the backbone of dementia care, making a critical yet often under-recognized contribution to the health system and society. In Canada alone, family caregivers or care partners provide an estimated 330 million hours of unpaid care annually, a figure projected to nearly double to 640 million hours by 2040 [5]. The economic value of this contribution is staggering; in 2016, the combined health system and out-of-pocket costs for people with dementia reached $10.4 billion, with unpaid caregiving accounting for a substantial proportion of this total [5]. By 2050, the annual hours of unpaid care provided by friends and family are expected to reach 1.4 billion—the equivalent of over 690,000 full-time jobs [2].

### Chronic Stress in Family Caregivers Associated with Higher Risk of Dementia

Caring for a person living with dementia is associated with substantial emotional, psychosocial, and financial burdens. Numerous studies have documented elevated rates of stress, anxiety, depression, and social isolation among family caregivers or care partners of people living with dementia [6,7]. A recent Canadian study found that 86% of those caring for both aging parents and their own children—sandwich generation caregivers—reported negative impacts on their health and well-being, including high levels of stress, exhaustion, and depressive symptoms [3]. Women constitute the majority of caregivers, and those who fall under the category of “sandwich generation” are particularly vulnerable to emotional distress and burnout, likely due to both cultural expectations and the hands-on nature of their caregiving roles [3,6]. Similarly, caregivers who are concurrently employed experience disproportionately high levels of stress combined with a low sense of mastery when faced with caring for mental and behavioral demands of older adults with dementia [8].

In particular, the chronic stress associated with dementia caregiving is a risk factor for increased risk of cognitive decline and dementia in caregivers themselves [7,9]. Prolonged exposure to caregiving stress is associated with elevated cortisol levels, immune dysregulation, and a greater incidence of cardiovascular disease and metabolic syndrome [9]. Furthermore, caregivers with high perceived stress are less able to engage in self-care, leading to a vicious cycle of declining health and reduced caregiving capacity [7]. Given these risks, interventions may need to consider both supporting caregivers in their roles but also addressing their own health and well-being. This is particularly crucial for family caregivers or care partners of people living with dementia who are burdened, stressed, and lacking the skills and knowledge to provide effective care.

### Evidence-Based Interventions for Family Caregivers or Care Partners of People Living with Dementia

A broad array of interventions has been developed to support family caregivers or care partners of people living with dementia, including support groups, counseling, psychoeducational programs, and respite care [10,11]. Among these, psychoeducational and multimodal structured psychotherapy have shown promise in reducing caregiver burden, stress, and depressive symptoms while enhancing caregiver competence and emotional resilience [7,12]. Structured programs that combine disease-specific knowledge, practical caregiving skills, psychotherapy, and emotional support have been shown to improve caregiver competence, reduce anxiety, and foster effective care strategies [7,8,13]. Multimodal interventions that integrate education, communication skills training, and problem-solving techniques offer a holistic approach to managing the complex demands of dementia care [12]. Support groups, whether in-person or online, foster a sense of community and shared understanding, reducing social isolation and promoting psychological well-being [11,14].

Despite their effectiveness, many traditional interventions are limited by in-person delivery models that can be difficult for caregivers to access regularly, especially those balancing work and/or living in rural and underserved communities. Barriers, such as time constraints, transportation challenges, and stigma, further impede engagement with support services. There is a need for innovative, accessible, and evidence-based interventions that can be delivered flexibly and at scale, particularly for caregivers who are most burdened, stressed, and at risk of declining health.

### Opportunity: Tech-Enabled Caregiver Support and Intervention

Simulation-based learning has long been a gold standard in professional health care education, offering a structured and psychologically safe environment to practice clinical skills, improve communication, and develop emotional intelligence [15]. Technologies, such as virtual reality (VR), can support the delivery of immersive simulation–based psychoeducation in an accessible, scalable, and engaging format. Recent studies have shown that VR-based training for both professional and family caregivers of people living with dementia can improve knowledge, compassion, and behavioral competence, in addition to supporting meaningful changes in caregiving practice [16]. Importantly, VR-based interventions can be designed to be self-paced and are potentially accessible from home or community settings, in urban or rural settings, offering flexibility and autonomy that are particularly valuable for caregivers juggling multiple responsibilities [16]. Interventions that include options for caregiver reflection, expert guidance, and resource linkage further enhance user experience and implementation potential [17-19]. Although evidence on effectiveness is still emerging, the preliminary findings are promising; immersive VR simulations can support empathy-building, skill acquisition, and confidence in care, all of which are central to caregiver preparedness, confidence, and well-being [19,20].

VR simulations not only enhance skill development but may also promote empathy by allowing caregivers to hear feedback from the character representing people living with dementia. When coupled with opportunities for guided reflection and clinical debrief, this form of intervention holds strong potential to shift caregiving behavior and improve caregiver outcomes. Moreover, as immersive technologies become more affordable and user-friendly, they represent a promising avenue for caregivers to access simulation-based, experiential learning and practice that is skills-based and emotionally engaging. However, few initiatives to date have rigorously explored the feasibility and acceptability of delivering simulation-based psychoeducation for family caregivers or care partners of people living with dementia through VR or evaluated its potential impact on caregivers’ psychosocial and mental health outcomes.

### VR-SIM Carers: Program at a Glance

The VR-SIM Carers Minimally Viable Prototype (MVP) is a self-paced, VR-based training tool designed to help family caregivers or care partners of people living with dementia develop practical caregiving strategies through immersive simulation–based learning. Developed using a co-design approach with input from older adults, caregivers, clinicians, simulation educators, and computer scientists, the MVP is accessible via commercially available headsets and aims to replicate real-world caregiving challenges, allowing users to learn and practice in a safe and controlled environment. The current prototype includes 3 interactive VR scenarios focused on challenging situations commonly encountered by family caregivers or care partners of people living with dementia. These scenarios are “high-fidelity,” meaning they closely replicate real-world caregiver situations with a high degree of realism. The content was inspired by real-life caregiver experiences discussed in a clinical setting during the Reitman Centre CARERS Program [8,21]. The 3 scenarios included in the MVP—Managing Apathy, Crisis Response, and Refusal of Care—were chosen through a priority setting survey completed by 16 knowledge users, family caregivers or care partners of people living with dementia and health or social providers and clinicians. Each scenario takes approximately 10 minutes to complete and may be repeated as needed. The further functionality of the MVP is detailed in the *Methods* section.

Psychoeducation is a therapeutic approach focused on educating individuals about their mental health conditions, treatments, and coping strategies, empowering them with essential knowledge for effective management. The development of our VR-based psychoeducational program adheres to the VR-CORE framework described by Birckhead et al [22], a set of guidelines and recommendations for the development and testing of VR treatments through 3 phases (VR1, VR2, and VR3), akin to the U.S. Food and Drug Administration’s Phase I-III framework for pharmaceuticals but adapted for VR. The objectives of this pilot study (see below) fit within the VR2 phase, which emphasizes early testing to assess the feasibility, acceptability, and tolerability of the VR intervention, along with its potential clinical efficacy. End user feedback will be obtained in order to explore the program’s readiness and identify implementation challenges. Our program targets outcomes, such as enhancing caregiver relationships with people living with dementia, boosting caregiver competency and resilience, and reducing caregiver stress.

### Research Objectives

The primary objective of the pilot study is to evaluate the feasibility, acceptability, and tolerability of immersive VR technology as a tool to deliver psychoeducation content to family caregivers or care partners of people living with dementia, as well as its readiness for implementation.

The secondary objective is to examine the initial efficacy of VR-based training in improving psychosocial outcomes of family caregivers or care partners of people living with dementia.

Attrition, missing surveys, and incomplete scale data will be treated as feasibility outcomes and reported transparently at each assessment time point. Quantitative analyses will primarily use available case summaries. Where appropriate, simple descriptive sensitivity analyses (eg, last observation carried forward or comparison of complete vs incomplete cases) may be conducted to assess the robustness of the observed trends. No formal imputation or model-based inference is planned, consistent with CONSORT recommendations for pilot and feasibility studies. Standardized assessment tools for depressive symptoms (Center for Epidemiological Studies Depression Scale) and caregiver burden (the Burden Questionnaire) are completed at baseline only and are intended as descriptive sample characteristics and contextual variables rather than outcomes or indicators of intervention effectiveness.

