### Power Calculation

Based on previous literature, a minimum sample size of 20 participants has been identified as appropriate for a pilot study to provide preliminary estimates of variability and to evaluate key feasibility parameters. These estimates are informed by existing caregiver pilot study interventions [24,25]. To account for expected attrition, a total sample size of 30 participants will be recruited. This target provides a buffer to maintain the minimum sample needed to evaluate feasibility outcomes and to estimate variance for future sample size calculations, while accounting for potential data loss due to loss to follow-up.

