#### Quantitative data

Descriptive statistics will summarize participants’ demographic characteristics and feasibility metrics. Statistical analysis will be completed using SPSS (version 29; IBM Corp) [37]. Paired 2-tailed *t* tests may be used to assess within-subject changes between specific time points as exploratory analyses. Repeated measures statistics will be used to describe change across the 3 time points. Consistent with CONSORT guidance for pilot and feasibility studies, caregiver outcomes (eg, competence, stress, resilience, empathy) are treated as exploratory, and no causal claims regarding intervention effectiveness will be made. Observed changes over time may reflect nonspecific effects such as time, expectancy, repeated measurement, or general study contact (eg, orientation and check-in calls). Repeated measures are collected to describe the direction and magnitude of change over time and assess the feasibility and sensitivity of the selected measures in this population and delivery format. All quantitative analyses are intended to estimate variability and inform sample size calculations and protocol decisions for a future definitive trial. A 2-sided *P* value of <.05 may be reported for descriptive purposes, but hypothesis testing is not the primary aim of this pilot.

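### The article gives conflicting analyses of the repeated caregiver scales; if dropout depends on observed scores they give different answers, and last observation carried forward cannot test robustness

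*Protocol article*

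**What the plan says.** Three places describe the analysis of the scales that Table 1 schedules at baseline, week 4 and one month.

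- **Abstract, Methods:** "Quantitative data will be analyzed using repeated-measures ANOVA and paired 2-tailed" t tests.
- **Methodological Approaches and Timeline:** "Quantitative analyses will primarily use available case summaries". The same paragraph adds "No formal imputation or model-based inference is planned" and offers, where appropriate, simple descriptive sensitivity analyses, the examples being "last observation carried forward or comparison of complete vs incomplete cases".
- **Data Analysis, Quantitative data:** repeated measures statistics of no named kind, with paired t tests as an option. It gives the purpose: "All quantitative analyses are intended to estimate variability and inform sample size calculations".

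On numbers, Power Calculation says "a minimum sample size of 20 participants has been identified as appropriate for a pilot study to provide preliminary estimates of variability", and then "To account for expected attrition, a total sample size of 30 participants will be recruited". It states no attrition rate.

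**The concern.** The named approaches use different people. Classical repeated-measures ANOVA drops anyone missing a visit. Available-case summaries use everyone seen at each visit, so unpaired visit means compare a fuller group at baseline with a reduced group later. Carry-forward uses everyone but fills unseen scores with old ones. An ANOVA with t tests also sits badly beside a statement that no model-based inference is planned.

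If those who leave differ from those who stay, the visit means and the ANOVA can disagree for reasons unrelated to the intervention. The article does not say which one supplies the direction, size and SD of change that it wants to hand to the next trial.

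**Working it through.** **1. Implied loss.** Keeping 20 after a loss d requires 20/(1 − d) recruits: 25 at 20%, 29 at 30%, 30 at 33.3% and 34 at 40%. The target of 30 therefore corresponds to one-third loss. The Progression Criteria count up to 20% loss as retention success and up to 40% as amendable. At one-third loss, about 30 people contribute at baseline and about 20 to the ANOVA.

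**2. Inputs the article does not give.** Effect, within-person correlation and dropout mechanism are assumptions here. Simulation: n = 30, three normal visits with SD 1, correlation 0.5, true change 0.30 SD at both later visits, about one-third loss, no return after dropout. Dropout was (a) random, (b) more likely with a high last observed score (logistic slope 1.5), or (c) more likely with a high unseen score (same slope). The likelihood column uses all observed scores with an unstructured covariance, as the proposed mixed model does.

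Estimated change, baseline to one month (truth 0.30):

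| Dropout | Unpaired available-case | Completers | Carried forward | Likelihood |
|---|---|---|---|---|
| (a) random | 0.29 | 0.30 | 0.24 | 0.30 |
| (b) on observed scores | 0.11 | 0.39 | 0.40 | 0.30 |
| (c) on unseen scores | 0.01 | 0.20 | 0.16 | 0.10 |

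Under (b) the errors are 0.11 − 0.30 = −0.19 for available-case and 0.39 − 0.30 = +0.09 for completers. A three-visit run with correlation 0.6 and no true change gives −0.21, +0.07, +0.11 (carried forward) and 0.00 (likelihood).

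**3. Range at 20% loss, mechanism (b).** With correlation 0.5: 0.19, 0.37, 0.38 and 0.31, in the same column order. With correlation 0.7: 0.14, 0.34, 0.34 and 0.31. The signs hold; available-case errors are −0.11 to −0.16 and completer errors +0.04 to +0.07.

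**4. SD of change (truth 1.00), one-third loss.**

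| Dropout | Completers | Carried forward | Likelihood |
|---|---|---|---|
| (a) | 0.99 | 0.91 | 0.99 |
| (b) | 0.96 | 0.90 | 0.98 |
| (c) | 0.97 | 0.88 | 0.98 |

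The carried-forward figure can be checked by hand. With random dropout, equal correlations and no mean change, only people lost before week 4 receive a change of exactly zero, so the SD ratio is √(1 − a), where a is the share lost before week 4. Equal loss per interval gives a = 1 − √0.667 = 0.18 and a ratio of √0.82 ≈ 0.90.

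Sample size scales with SD². 0.91² = 0.83, 0.90² = 0.81 and 0.88² = 0.77, so a plan based on the carried-forward SD would be 17% to 23% too small.

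**5. Carry-forward as a robustness check.** Under (b), completers give 0.39 and carry-forward 0.40. Their agreement would look reassuring, yet both are about 0.1 SD too high.

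**6. Precision at n = 30.** Under random dropout, the sampling SD of the estimated change is 0.225 (available-case), 0.233 (completers) and 0.218 (likelihood), so the likelihood analysis costs nothing. Under (b) it is 0.234, 0.222 and 0.237. Root mean square error is then √(0.19² + 0.234²) ≈ 0.30, √(0.09² + 0.222²) ≈ 0.24 and 0.24.

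**The case against.** The strongest reply is that this is a small single-arm pilot with a deliberately descriptive plan. The outcomes are labelled exploratory and causal claims are disclaimed. Attrition is itself a feasibility outcome, reported at each time point, and losses are reported with reasons. The P value "may be reported for descriptive purposes, but hypothesis testing is not the primary aim of this pilot". No progression criterion uses a change score, an SD or a P value. Model details commonly belong in an analysis plan that is not shown. All of this stands and limits the importance of the point. It does not explain why the Abstract and the Methods name different analyses, nor remove the need for a usable change and SD when estimating variability is the stated purpose. The phrase on model-based inference may have been aimed at missing-data models only; if so, it should say so.

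Several stronger readings are tempting, and the documents do not support them.

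- A reader might infer that every listed method is biased whenever people drop out. Under random dropout, available-case and completer estimates are unbiased.
- A reader might infer that the next trial would be sized on a carried-forward SD. Carry-forward is only an example of an optional sensitivity analysis; no such use is proposed.
- A reader might expect an SD shrinkage near 20%. That figure, √0.667 ≈ 0.82, needs everyone to be lost before week 4. With losses spread over both intervals it is about 10%.
- A reader might take available-case to mean unpaired throughout. The optional paired t tests compare the same people; from baseline to one month, with no return after dropout, they match the completer result.
- A reader might take the mixed model as a cure. Under mechanism (c) it gives 0.10, further from 0.30 than completers (0.20), though closer than unpaired available-case means (0.01).

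Sampling error at this size is also as large as most of the biases. Against completers, the model's gain under (b) is in bias, with almost no gain in root mean square error. Carry-forward has a smaller sampling SD (0.169 under (b)), but only because it substitutes old scores for unseen ones.

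**Conclusion.** The point holds in limited form. The Abstract, the missing-data paragraph and the Quantitative data section conflict and must be reconciled. At the implied one-third loss, with dropout depending on observed scores, unpaired available-case means err by about −0.2 SD and completers by about +0.1 SD; under random dropout neither is biased. Carry-forward cannot show robustness and understates the SD of change by about 10%. The completer SD is at most about 4% low.

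The sizes depend on assumed correlation, effect and dropout strength, and the signs on high scorers being the ones who leave. That the ANOVA uses completers only is inferred from the classical method; the article states no analysis set. The effect is confined to the exploratory caregiver outcomes. The optional P value is a minor matter.

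**What to change.** - Make the Abstract, the missing-data paragraph and the Quantitative data section say the same thing, and remove the repeated-measures ANOVA wording.
- For each scale measured three times, estimate change from one linear mixed model on all observed scores: visit as a categorical effect, unstructured within-person covariance, REML, and a simpler covariance if it does not converge. State the missing-at-random assumption.
- Report mean change with a 95% confidence interval, the SD and the between-visit correlations, with available-case means and their n beside them.
- Remove last observation carried forward. Keep the comparison of complete and incomplete cases, which bears directly on selective dropout.

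The cost is a few lines of text and code, with no new data and no change to the target of 30. The downside is a slightly more complex model in a small sample, still biased if dropout depends on unseen scores. The change should be made before the analysis, which the article expects to complete in April 2026.
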